[figure not shown]

## Research Protocol Template (Low Risk Research Project and Clinical Audits)

A well written and complete protocol is essential for a high quality research project. A study protocol generally follows a conventional layout. There are several templates already available although most are developed for commercially-sponsored randomised controlled studies. This research protocol template aims to offer Northern Health surgical medical, nursing, midwifery and allied health researchers a more generic guide suitable for a broader range of scientific research enquiries.

The preparation of a protocol is an important first step in the research process for the following reasons:

1. It states the research question you aim to answer;
2. It encourages adequate consideration and planning of project detail *before* you begin;
3. It allows co-investigators or peers a living and dynamic document for contribution and early review prior to its completion;
4. It acts as a record and reminder for you and your supervisor (co-investigator or co-worker) of the initial project aims and stated procedures. This record also enables you to monitor the progress of your project; and
5. It provides the basis for funding or human research ethics applications.

When drafting your protocol:

- Discuss project design and scope with supervisors/peers.
- Discuss appropriate statistical analysis methods with a statistician.
- Delete sections that are not applicable.
- Add version number and document date in the footer.

[figure not shown]

**1. INTRODUCTION**

Current standard practice for lower limb arterial assessment to determine the presence of peripheral arterial disease includes the use of a toe brachial index (TBI), whereby the toe systolic blood pressure is divided by the brachial systolic blood pressure. Anecdotal evidence suggests that due to patient convenience clinicians often assess TBIs during haemodialysis. Historically this has not taken into consideration the fact that those with CKD on haemodialysis can experience changes in their systolic blood pressure during dialysis, which is known as intradialytic hypertension and intradialytic hypotension. These changes may in turn affect the results of toe brachial index.

Currently it is not known if dialysis affects toe systolic pressures. This study will aim to monitor both brachial and toe systolic blood pressures to obtain TBI results, with measurements taken at specific time intervals (pre-dialysis, during dialysis (hourly) and post-dialysis) to monitor the association between the two. These results may then be applied to clinical practice to determine the suitability of completing TBI assessments during dialysis. This information will guide clinical practice, as these assessments guide decisions regarding sharp debridement, and wound dressing selection.

**2. BACKGROUND**

Individuals with chronic kidney disease (CKD), including those with end-stage kidney disease (ESKD) receiving haemodialysis treatment are at inordinate risk of lower limb ulcerations, infection, and amputations compared to individuals in the general population with normal

[figure not shown]

renal function (Ishioka et al., 2018). For patients on dialysis - apart from a history of prior ulceration or amputation - the greatest risk factors for ulceration are peripheral arterial disease (PAD), neuropathy, and cerebrovascular disease (Kaminski 2019). Peripheral arterial disease is highly prevalent in ESKD. Patients with CKD often have one or more risk factors associated with PAD such as older age, smoking, diabetes, hypertension and hyperlipidemia. CKD itself imposes greater additional risk due to chronic inflammation, hypoalbuminemia, and a pro-calcific state (Garimella et al, 2014). Almost all patients with end-stage kidney disease have evidence of peripheral neuropathy, although clinical burden is greatest in those with concurrent diabetes (Arnold 2017). There is a need to identify patients at risk of ulceration and amputation, and when ulceration occurs prevent progression, amputation or re-ulceration.

According to the International Working Group on the Diabetic Foot guidelines on Peripheral Arterial Disease (<https://iwgdfguidelines.org/wp-content/uploads/2019/05/04-IWGDF-PAD-guideline-2019.pdf>) first line assessment to determine the presence of PAD is to compile a detailed relevant medical history and palpate pedal pulses. For patients in high risk groups, these steps alone are not reliable enough to exclude PAD, and subsequent screening assessments should be performed (Hinchcliff et al., 2019). This may include evaluation of pedal Doppler arterial waveforms in combination with performing an Ankle Brachial Index (ABI) or toe brachial index (TBI). ABIs are calculated by measuring the systolic blood pressure at the ankle and dividing it by the systolic blood pressure at the arm. Alternatively, TBIs are calculated by measuring the systolic blood pressure at a toe and dividing it by the systolic blood pressure at the arm.

The ABI has been shown to be both specific and sensitive in the diagnosis of PAD (Hinchcliff et al., 2019) however in some patients it may yield a falsely elevated result due to the presence of medial artery calcification, a condition common to people in the advanced stages of both diabetes and CKD. In this case, it is preferable to measure toe systolic pressure and conduct a TBI. There is no single measure that has been shown to provide an optimal assessment of risk of PAD, however PAD is less likely when an ABI is between 0.9-1.3; toe pressure measurements are higher than 30mmHg; or when a TBI is higher than 0.75, and Doppler waveforms are triphasic. Using more than one of these tests in parallel enables clinicians to make a more accurate diagnosis. Recent research has suggested that the use of pedal Doppler arterial waveforms in combination with TBI is the superior lower limb arterial assessment (Brownrigg et al., 2016). Clinical guidelines recommend that patients undergoing ABI, TBI and audible doppler assessments are seated for at least 20 minutes prior to assessment (Hinchcliff et al., 2019).

Expert evaluation for PAD including use of TBI is also standard-of-care in the management of foot ulcers in high-risk patients such as those with ESKD. PAD can alter the body's ability to heal a foot ulceration, and can lead to infection, increased tissue loss and insufficient delivery of nutrition, oxygen and antibiotics, all of which can lead to further foot amputation (Amin and Doupis, 2016). The presence of PAD needs to be promptly excluded so that clinicians can safely perform adequate ulcer treatment including sharp debridement to assist with wound preparation. It is also necessary to have this information in order to decide whether a dry or moist wound dressing is suitable to treat a DFU (Roelsing and Andrews, 2019).

Due to the great demands on patient times of haemodialysis, it is common for podiatry assessment and treatment to occur opportunistically during dialysis sessions. However, there has been no systematic evaluation of the impact of haemodialysis and in particular changes in blood pressure during dialysis may affect the measurement of TBI. Blood pressure is routinely measured before, during and after haemodialysis and patients may experience an fall in blood pressure during or immediately after haemodialysis known as intradialytic hypotension (Sars B et al., 2020) or a paradoxical increase in blood pressure known as intradialytic hypertension (Van Buren and Inrig, 2016). Pre-dialysis systolic blood pressure is typically around 10mmHg higher than intradialytic blood pressure and post-dialysis systolic blood pressure is around 10mmHg less than intradialytic blood pressure (Sterns et al., 2014). When intradialytic hypertension occurs, it is most common in the second or third hour of hemodialysis, and after significant ultrafiltration has taken place (Inrig, 2009). During dialysis blood is also diverted to an extracorporeal circuit, which may result in contraction of blood vessels to maintain blood pressure.

The results of this research will aim to assist clinicians with clinical guidelines around arterial assessments and also wound management for those undergoing haemodialysis.

### **3. AIM(S) AND OBJECTIVES OF STUDY**

The aim of this study is to evaluate toe brachial indices, during haemodialysis, in participants with end stage kidney disease.

### **4. RESEARCH PLAN/METHODOLOGY**

#### **4.1 Participants**

Selection criteria:

30 participants with chronic kidney disease undergoing haemodialysis will be recruited from Northern Health Dialysis Satellite Clinics at Northern Hospital Epping, Craigieburn Centre and Broadmeadows Hospital. Participants will have been admitted as same-day inpatients. Participants will be excluded if they have cognitive impairment or are under 18 years of age. Participants speaking any language will be included and interpreters used as required.

Participant/data (de-)identification procedures:

Identifiable patient data will be replaced with a code/unique number. The master list of names and matching codes will be stored electronically and password protected by the PI.

#### **4.2 Measures**

The primary outcomes for this study will be toe brachial index, measured pre-dialysis, during dialysis (at 1, 2, and 3 hours), and post-dialysis.

Additional measures will include routinely collected clinical data:

- each timepoint: ultrafiltration (fluid-removal) rate, and dialysis blood flow rate

[figure not shown]

- Each session: pre- and post-dialysis weight, requirement for fluid bolus for symptomatic intradialytic hypotension
- Each subject – demographic data, history of current ulceration, prior amputation, prior ulceration, PVD, revascularization for PVD, diabetes, diagnosed peripheral neuropathy.

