### 4.4 STATISTICAL CONSIDERATIONS

The sample size has not been able to be guided based on published information, as no details relating to the variance from patient to patient in the change in toe brachial indices over time can be found. Stern (2014) indicates that the pre-dialysis and post-dialysis systolic

blood pressure are found to be 10 mm Hg more and 10 mm Hg less than the interdialytic blood pressure respectively [13], but there is no indication of the variance from patient to patient in the change in toe brachial indices over time. Thus, the sample size of n=30 patients has been selected as being able to be conducted effectively within the timeframe of the study. This will then indicate if additional sample is required to address the needs of the study.

Descriptive analysis will be conducted to summarise the toe brachial index results over the study timepoints for each patient. Data will be presented as means (standard deviations) if normally distributed or as median (inter-quartile ranges) if skewed. The mean of changes from one timepoint to the next are likely to be normally distributed, and thus the data will be assessed using paired t-tests. More detailed analysis, including longitudinal analysis using mixed-effects linear regression models may be explored if the sample size allows an investigation of the effects of some patient characteristics. A p-value of less than 0.05 will indicate statistical significance, with the data to be compiled in Microsoft Excel and analysed using Stata version 15.1 (StataCorp, College Stations, Texas, USA).

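### Toe and brachial pressures are recorded to form the TBI, but no named outcome or analysis separates them, although the stated unknown is the effect of dialysis on toe pressure

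*Protocol*

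**What the plan says.** The Introduction (section 1) states the gap in terms of toe pressure: "Currently it is not known if dialysis affects toe systolic pressures". It continues: "This study will aim to monitor both brachial and toe systolic blood pressures to obtain TBI results". It adds that the relation between the two pressures will be followed before, during and after dialysis. TBI is defined there as a ratio, in which "toe systolic blood pressure is divided by the brachial systolic blood pressure".

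The formal aim in section 3 concerns the ratio: "The aim of this study is to evaluate toe brachial indices, during haemodialysis, in participants with end stage kidney disease".

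Section 4.2 sets the outcome: "The primary outcomes for this study will be toe brachial index, measured pre-dialysis, during dialysis (at 1, 2, and 3 hours), and post-dialysis". The additional measures at every timepoint are given as "each timepoint: ultrafiltration (fluid-removal) rate, and dialysis blood flow rate". Neither toe nor brachial pressure is listed as an outcome or an additional measure.

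Section 4.4 says: "Descriptive analysis will be conducted to summarise the toe brachial index results over the study timepoints for each patient". It then plans paired t-tests on changes between successive timepoints, and possibly mixed models. It names no other variable for analysis over time.

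Two statements in the Background (section 2) bear on this. Toe pressure has its own diagnostic line (30 mmHg), given separately from the TBI line (0.75). Systolic pressure is also expected to move: "Pre-dialysis systolic blood pressure is typically around 10mmHg higher than intradialytic blood pressure", with the post-dialysis value about 10 mmHg below the intradialytic one.

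**The concern.** A ratio moves when its numerator moves, when its denominator moves, or both. The protocol already expects the denominator to fall across a session. If only TBI is analysed, a rise in TBI could come wholly from brachial pressure, and a flat TBI could conceal equal proportional falls in both pressures. Either way, the question raised in the Introduction, whether toe pressure itself changes, would go unanswered by the analysis as written. The promised look at how the two pressures relate is not carried into sections 4.2 or 4.4. If the components were examined only after the TBI results were known, that examination would be post hoc.

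**Working it through.** The protocol gives no figure for the expected TBI change. The sample size of 30 was chosen for feasibility, so there is no calculation to reproduce. The check is whether the brachial change that the protocol expects is large enough to matter.

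**Inputs from the protocol**
- TBI = toe systolic / brachial systolic (section 1).
- Systolic pressure is about 10 mmHg above a reference level before dialysis and 10 mmHg below it afterwards. Section 2 calls the reference intradialytic and section 4.4 calls it interdialytic. The pre-to-post gap is 10 + 10 = 20 mmHg under either wording. A 10 mmHg step during dialysis follows only from section 2, so it is not used here.

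**Assumptions, because the documents give no values**
- The quoted systolic changes apply to the brachial pressure used for TBI.
- Baseline brachial pressure B is 130 to 160 mmHg, and baseline TBI r is 0.50 to 0.75. Baseline toe pressure is then r × B.

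**Case 1: toe pressure unchanged, brachial pressure down 20 mmHg**

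Change in TBI = rB/(B − 20) − r = 20r/(B − 20).
- Smallest: 20 × 0.50/140 = 0.071 (B = 160).
- Largest: 20 × 0.75/110 = 0.136 (B = 130).
- Mid-range: toe 98 mmHg and brachial 140 to 120 mmHg gives 98/140 = 0.70 and 98/120 = 0.817.

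A rise of this size can cross the 0.75 line with no change at the toe: 91/140 = 0.650 and 91/120 = 0.758. The value of 91 mmHg was picked to lie near the line, so this shows what is possible, not what is typical.

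**Case 2: toe pressure falls in proportion, so TBI does not change**

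Hidden toe fall = rB − r(B − 20) = 20r.
- Range: 20 × 0.50 = 10 mmHg to 20 × 0.75 = 15 mmHg, whatever B is.
- Mid-range: toe 98 to 84 mmHg and brachial 140 to 120 mmHg gives 98/140 = 84/120 = 0.70.

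**Simulation at n = 30**

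Setup: 2,000 runs; two-sided paired t-test at 0.05 on one pre-to-post change; baseline brachial 140 (SD 20) mmHg; baseline TBI 0.70 (SD 0.15); brachial pressure multiplied by 120/140; noise SD of 8, 12 or 16 mmHg in each pressure change. All these values are assumed except n, the 0.05 level and the 20 mmHg fall.

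| Truth | TBI test rejects | Toe pressure test rejects |
|---|---|---|
| Toe falls in proportion | 5–7% | 99–100% |
| Toe unchanged | 97–100% | 4–5% |

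In these two scenarios the TBI test and the toe pressure test give opposite answers. Section 4.4 plans changes between successive timepoints, so the 20 mmHg would be spread over four steps and each single test would see less of it. The algebra of masking is the same at each step.

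**What would separate the two**

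Change in log TBI = change in log toe − change in log brachial. In case 1: 0 − ln(120/140) = 0.154, which equals ln(0.817/0.70). In case 2: ln(84/98) − ln(120/140) = −0.154 + 0.154 = 0.

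**The case against.** The strongest reply is that TBI is the right outcome for this study. The aim in section 3 concerns TBI, and the clinical use named in section 1 is whether TBI can be assessed during dialysis. For that purpose, a shift caused only by the brachial denominator is part of the answer, because it shows that the result depends on when it is taken. This stands, and TBI should remain primary.

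A reader might infer that the study is unable to separate the two pressures. The documents do not support that. Both must be recorded to form the ratio, and section 1 says both will be monitored. Only the named outcome and analysis are missing.

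A reader might also infer that a purely brachial change would be reported as a change in limb perfusion. Nothing in the protocol commits to that reading. Section 1 itself says that changes in systolic pressure during dialysis may alter the TBI.

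It can also be said that component summaries may sit in a statistical analysis plan that is not shown, and that the list of additional measures is worded openly. This has some force for the analysis detail, and for brachial pressure, which section 2 describes as routinely measured. It has less force for toe pressure. Section 4.2 is where the protocol declares its outcomes, and toe pressure, the subject of the stated gap, is not there.

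**Conclusion.** The point holds as a mismatch between the protocol's stated rationale and its declared outcomes. It is not a flaw in the choice of TBI or in the data to be collected. Followed as written, the analysis leaves the toe pressure question unanswered.

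The size is material at the protocol's own expected brachial change. A 20 mmHg pre-to-post fall raises TBI by about 0.07 to 0.14 with the toe unchanged, or conceals a proportional toe fall of 10 to 15 mmHg. These ranges rest on assumed baselines (brachial 130 to 160 mmHg, TBI 0.50 to 0.75), and the simulated rejection rates also rest on assumed variability. The possibility of masking rests on neither, since it follows from the definition of the ratio. How toe pressure actually behaves during dialysis is not known from the documents, so neither scenario is a prediction.

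This is an inexpensive improvement that should be made, and it does not threaten the validity of the TBI results.

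**What to change.** - **Section 4.2:** keep TBI as the primary outcome. Add toe systolic pressure and brachial systolic pressure at each of the five timepoints as secondary outcomes.
- **Section 4.4:** analyse each pressure with the same paired contrasts as TBI. Report mean change with a 95% confidence interval, labelled secondary.
- **Optional:** report changes in log toe, log brachial and log TBI, so that a shift in log TBI is divided exactly between its two parts. The division is exact for log TBI only, not for the arithmetic TBI change that the planned t-tests use.

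**Cost.** No new measurements are needed and the sample size does not change. Five timepoints give four successive changes, so two added outcomes bring 2 × 4 = 8 further comparisons, making 12 in all with the 4 for TBI. At n=30 these are best read as estimates with intervals and not as further significance tests.

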### 4.3 Procedures

#### Consent process(es):

All participants to be consented will be directly approached by the PI (BB) to participate in the study. The PI or one of the research assistants will arrange a screening for eligibility with each patient and arrange data collection on a suitable day that the participant will be undergoing dialysis at a NH satellite clinic. Once the participant has been informed and verbally consented to participate, written information and a consent form will be provided.

#### Details of data collection, processing and analysis :

Patients attending NH dialysis service will be approached over six months until 30 participants are recruited. The PI or research assistant will only approach those patients who are determined by the dialysis nurses as being clinically appropriate to participate based on the inclusion criteria. Written, informed consent will be obtained prior to each assessment by a study investigator who is an employee of NH (BB).

TBIs will be completed on each participant pre-dialysis, at hourly intervals during dialysis, and post-dialysis.

#### Record keeping procedures, including storage of data access and destruction:

The patient data will be kept strictly confidential according to the National Statement on Ethical Conduct in Human Research 2007 and the Australian Code for Responsible Conduct of Research 2007.

- Consent forms will be scanned into CPF under admission date. The hard-copy version will be kept by the PI and research team in the Foot Procedure Room (key access required) in a locked cupboard and a copy will be given to participants.
- All recorded data will be saved on a NH password protected computer, and will only be accessed by named investigators.
- Patients who participate will be re-identifiable by linking de-identified information with an 'auxiliary dataset' that contains identifying information. The de-identified information and the auxiliary dataset will be kept in separate password encrypted files on Northern Health shared drive. Patient data will be only be transferred and analysed in a coded form.
- Individual patients will not be identifiable from the presented or published material.

### 4.4 STATISTICAL CONSIDERATIONS

The sample size has not been able to be guided based on published information, as no details relating to the variance from patient to patient in the change in toe brachial indices over time can be found. Stern (2014) indicates that the pre-dialysis and post-dialysis systolic

blood pressure are found to be 10 mm Hg more and 10 mm Hg less than the interdialytic blood pressure respectively [13], but there is no indication of the variance from patient to patient in the change in toe brachial indices over time. Thus, the sample size of n=30 patients has been selected as being able to be conducted effectively within the timeframe of the study. This will then indicate if additional sample is required to address the needs of the study.

Descriptive analysis will be conducted to summarise the toe brachial index results over the study timepoints for each patient. Data will be presented as means (standard deviations) if normally distributed or as median (inter-quartile ranges) if skewed. The mean of changes from one timepoint to the next are likely to be normally distributed, and thus the data will be assessed using paired t-tests. More detailed analysis, including longitudinal analysis using mixed-effects linear regression models may be explored if the sample size allows an investigation of the effects of some patient characteristics. A p-value of less than 0.05 will indicate statistical significance, with the data to be compiled in Microsoft Excel and analysed using Stata version 15.1 (StataCorp, College Stations, Texas, USA).

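### Apart from pre-dialysis versus 1 h, no firmly planned test compares a later TBI reading (2 h, 3 h, post) with the pre-dialysis TBI

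*Protocol*

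**What the plan says.** Protocol section 4.2 makes the primary outcome "toe brachial index, measured pre-dialysis, during dialysis (at 1, 2, and 3 hours), and post-dialysis", which is five readings per patient.

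Section 4.4 describes three layers of analysis:

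- A descriptive summary of TBI over the timepoints, with no test.
- Paired t-tests, introduced with this reasoning: "changes from one timepoint to the next are likely to be normally distributed, and thus the data will be assessed using paired t-tests".
- A conditional extension: "longitudinal analysis using mixed-effects linear regression models may be explored if the sample size allows an investigation of the effects of some patient characteristics".

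The threshold is set by "A p-value of less than 0.05 will indicate statistical significance". No reference timepoint and no primary contrast is named. On size, "the sample size of n=30 patients has been selected as being able to be conducted effectively within the timeframe of the study", and on variability the protocol says that "there is no indication of the variance from patient to patient in the change in toe brachial indices over time".

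The purpose is given in section 1: "These results may then be applied to clinical practice to determine the suitability of completing TBI assessments during dialysis". Section 2 adds a reason to look at the later hours: "When intradialytic hypertension occurs, it is most common in the second or third hour of hemodialysis".

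**The concern.** Judging whether a TBI taken on dialysis is suitable means comparing it with one taken off dialysis. The natural contrasts are 1 h, 2 h and 3 h, and also post-dialysis, each against pre-dialysis. The contrast written into section 4.4 is a different one: each reading against the reading before it. Of the four resulting tests, one involves the pre-dialysis value.

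Two misreadings could follow. If TBI moves gradually, the total change is cut into small steps, and each may be non-significant while the 3 h reading has moved well away from pre-dialysis. Conversely, a significant change from 2 h to 3 h would not say whether either reading departs from pre-dialysis. Section 1 says that these assessments guide debridement and dressing decisions, so a reassuring statement that TBI did not change significantly between timepoints would carry weight.

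This is not detail left to a later analysis plan. The protocol does state a contrast, and that contrast does not fit its stated purpose.

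**Working it through.** **Which contrasts are tested.** Five timepoints give four successive pairs out of 5 × 4 / 2 = 10 possible pairs.

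| Contrast with pre-dialysis | Firmly tested under section 4.4? |
|---|---|
| 1 h | Yes (first successive pair) |
| 2 h | No |
| 3 h | No |
| Post | No |

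This part depends on no assumed number.

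**Inputs for the size.** From the protocol: n = 30 and a significance level of 0.05. Assumed: two-sided tests, an SD of 0.10 for the change between two successive readings, and a steady drift of 0.02 per step. The protocol states no power, effect size or SD, so it has no figure to reproduce.

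**Formula.** The power of a paired t-test with standardised change d is P(|T| > 2.045), where T is noncentral t with 29 degrees of freedom and noncentrality d × √30. At n = 30, 80% power needs d = 0.53, which is a change of 0.053 if the SD is 0.10.

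An unknown correlation structure governs the SD of a change over k steps, so two cases are used:

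- Equal correlation: the SD stays at 0.10 for every pair, so d = 0.2 × k.
- Independent increments: the SD grows as 0.10 × √k, so d = 0.2 × √k.

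| Test | Mean change | d, equal correlation | Power | d, independent increments | Power |
|---|---|---|---|---|---|
| Any one successive pair | 0.02 | 0.20 | 0.185 | 0.20 | 0.185 |
| 2 h vs pre | 0.04 | 0.40 | 0.56 | 0.28 | 0.32 |
| 3 h vs pre | 0.06 | 0.60 | 0.89 | 0.35 | 0.45 |
| Post vs pre | 0.08 | 0.80 | 0.99 | 0.40 | 0.56 |
| Mean of 1–3 h vs pre | 0.04 | 0.49 | 0.74 | 0.32 | 0.40 |

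For the last row, the SD is 0.10 × √(2/3) = 0.082 under equal correlation. Under independent increments it is 0.10 × √(14/9) = 0.125.

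**Other drifts** (per step, in units of the one-step SD; ranges run from independent increments to equal correlation):

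| Drift per step | One successive test | 3 h vs pre | Post vs pre | At least one of four successive |
|---|---|---|---|---|
| 0.10 | 8% | 15–36% | 19–56% | 29% |
| 0.15 | 12–13% | 28–66% | 36–89% | 42–44% |
| 0.20 | 18–19% | 45–89% | 56–99% | 56–61% |
| 0.25 | 26% | 63–98% | 75–100% | 71–78% |

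**Price of the any-of-four reading.** With no drift, the chance that at least one of four unadjusted tests is significant is 1 − 0.95⁴ = 0.185 if they are independent, and 0.17 in simulation under equal correlation.

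**A different shape.** Suppose TBI moves by 0.06 between pre-dialysis and 1 h and by another 0.06 between 3 h and post, with no change in between. Each of those two successive tests then has d = 0.6 and power 0.89, as good as 3 h versus pre-dialysis under equal correlation (0.89) and better than it under independent increments (0.45).

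**The case against.** Several points on the other side have force.

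- A reader might infer that no planned test sets a dialysis reading against pre-dialysis. The protocol does not support that: pre-dialysis to 1 h is such a test. The gap is confined to 2 h, 3 h and post.
- The mixed model could supply the missing contrasts. But it only may be explored, depends on the sample size, and is directed at patient characteristics. It does not commit the study to any comparison with pre-dialysis.
- The descriptive summary covers all timepoints, so a drift would be visible in the means. That is true, but the plan attaches no inference to it.
- The phrase about successive timepoints sits in a remark on normality and might loosely mean any two timepoints. That reading leaves ten pairs with none named as primary, so the sentence would still need rewording.
- Steady drift is an assumption. The only pattern given in sections 2 and 4.4 is for systolic pressure: about 10 mmHg higher before dialysis and about 10 mmHg lower after it than the intradialytic value. If TBI followed that shape, the steps would fall on pairs that are tested and little would be lost. The protocol predicts no shape for TBI, which is a ratio, and the remark on the second and third hours concerns intradialytic hypertension. This stands as a limit on the size of the problem.
- At least one of the four successive tests is significant in 56% to 61% of trials at a drift of 0.02, which matches or exceeds post versus pre-dialysis under independent increments (56%). This also stands, but that rule carries a false-positive rate of 17% to 19% and does not show which reading departs from pre-dialysis.
- The formal aim in section 3 is only to evaluate TBI during haemodialysis, and the study is feasibility-sized. All five readings are collected, so every contrast stays computable. This lowers the cost of the defect but does not make the stated contrast the right one.

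**Conclusion.** The point holds. Read plainly, section 4.4 firmly tests only successive changes, and three of the four contrasts with pre-dialysis are left out, although section 1 wants the results to inform the suitability of TBI during dialysis. That mismatch does not depend on any SD or correlation.

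The loss of power does depend on them. For a steady drift of 0.02 per step with an assumed one-step SD of 0.10, a single successive test has about 18% power, against 45% to 89% for 3 h versus pre-dialysis and 56% to 99% for post versus pre-dialysis. A reader might infer that the upper figures apply generally. They need roughly equal correlation between all readings, which the protocol neither states nor can support. A reader might also infer that the plan is bound to miss a real effect. It is not: abrupt changes at the start and end of dialysis would be picked up.

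**What to change.** In section 4.4, define the planned paired comparisons as the change from pre-dialysis at 1 h, 2 h, 3 h and post-dialysis, by paired t-tests or a mixed model with time as a factor. Name one primary contrast, for example the mean of the 1 h to 3 h readings minus pre-dialysis, or 3 h minus pre-dialysis. Report estimates with 95% confidence intervals, treat the remaining contrasts as secondary, and keep successive changes as description.

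Under the steady-drift assumption above, the mean contrast has 40% to 74% power and the 3 h contrast 45% to 89%. The mean contrast uses all the intradialytic readings, while the 3 h contrast is more sensitive to a late change.

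The cost is a short rewording, with the same patients, readings and software. Successive changes lose their status as formal tests, and one contrast must be chosen before the data are seen.
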